## Abstract

**Background:**

The aim of the study; *LCoMotion – Learning, Cognition and Motion* was to develop, document, and evaluate a multi-component physical activity (PA) intervention in public schools in Denmark. The primary outcome was cognitive function. Secondary outcomes were academic skills, body composition, aerobic fitness and PA. The primary aim of the present paper was to describe the rationale, design and methods of the LCoMotion study.

**Methods/Design:**

LCoMotion was designed as a cluster-randomized controlled study. Fourteen schools from all five regions in Denmark participated. All students from 6^th^ and 7^th^ grades were invited to participate (n = 869) and consent was obtained for 87% (n = 759). Baseline measurements were obtained in November/December 2013 and follow-up measurements in May/June 2014. The intervention lasted five months and consisted of a “package” of three main components: PA during academic lessons, PA during recess and PA homework. Furthermore a cycling campaign was conducted during the intervention period. Intervention schools should endeavor to ensure that students were physically active for at least 60 min every school day. Cognitive function was measured by a modified Eriksen flanker task and academic skills by a custom made mathematics test. PA was objectively measured by accelerometers (ActiGraph, GT3X and GT3X+) and aerobic fitness assessed by an intermittent shuttle-run test (the Andersen intermittent running test). Furthermore, compliance with the intervention was assessed by short message service (SMS)-tracking and questionnaires were delivered to students, parents and teachers.

**Discussion:**

LCoMotion has ability to provide new insights on the effectiveness of a multicomponent intervention on cognitive function and academic skills in 6^th^ and 7^th^ grade students.

**Trial registration:**

Clinicaltrials.gov: NCT02012881 (10/10/2013)

## Background

Prevalence of obesity and overweight is increasing among children and adolescents throughout the world [1]. At the same time it has been shown that physical activity (PA) and aerobic fitness have decreased particularly in the less fit pediatric population [2–4]. Taken together, the health consequences of these trends may be a future adult population with high prevalence of obesity and metabolic abnormalities [5].

PA has been suggested as an important factor in prevention of both obesity and lifestyle diseases [5–7]. Schools provide an advantageous setting for encouraging a healthy lifestyle among children and for enhancing PA [8], since school interventions can reach children from all risk groups [9], while stigmatization of children at risk likely is avoided. Previous school-based intervention studies addressing different health related outcomes have been inconclusive regarding results on body composition [10], PA [11–13] and aerobic fitness [11, 13]. Even though many of the school-based intervention studies found some improvements in health parameters, there still seems to be a lack of willingness of parents, teachers and politicians in many countries to prioritize PA during the school day. However, recent research has shown that PA and a high aerobic fitness level are associated not only with metabolic health, but also with improved cognitive function and academic skills [14–18]. If these results could be confirmed and expanded, it might change the priorities in different school systems towards more PA during the school day. Childhood is probably the most important time of life for development of cognitive skills, and given the assumed positive association with PA, it emphasizes the importance of early intervention to decrease inactivity and/or improve PA. On this basis, the Danish government has decided that every child in public schools should have 45 min of PA every school day starting from summer 2014 [19]. Some school-based interventions have already been conducted with the aim of investigating the effect of increased PA on cognitive function and/or academic skills [20–24]. Some of these studies were, however, small-sized [22–24], the analyses of the effect on academic skills were only performed on a sub-sample of the participants [21], or the study was not conducted as a randomized controlled trial [24]. With these limitations kept in mind, there seems to be a positive effect or at least no negative effect of taking time from academic subjects and directing it towards more PA. However, the most effective way to compose school-based interventions is still unknown. One challenge is to design an intervention which is effective in terms of improving health and cognitive function of children, while at the same time possible to implement in large scale school settings.

The overall objective of the present study; *LCoMotion – Learning, Cognition and Motion,* was therefore to evaluate the effect of a school-based PA intervention aiming at increasing PA to a total of 60 min per school day. LCoMotion is the first large school-based PA-intervention in Denmark assessing cognitive function and academic skills, as well as body composition, aerobic fitness and PA. The primary aim of the present paper is to describe the rationale, design and methods of the LCoMotion study.

## Methods/Design

### Study design

LCoMotion is a cluster randomized controlled intervention study including students from the 6^th^ and 7^th^ grade at public schools in Denmark (12-14 years old). The clusters consisted of participating schools. Schools were randomly allocated either to the intervention or control group. After the follow-up measurements all control schools received the same intervention "package" as the intervention schools.

### Recruitment and randomization

A complete chart illustrating the recruitment and randomization process is shown in Figure 1. Baseline measurements were done in November/December 2013, follow-up measurements in May/June 2014. Data analysis has not yet been completed. All schools participating in a primary-school project about PA and health (Styr på Sundheden [25]) were invited to participate in LCoMotion. Out of 20 schools, 13 schools accepted the invitation. Schools were randomly assigned to receive either the intervention "package" or serve as controls. Two intervention schools withdrew the acceptance before the start of the study, but after the randomization. Additionally three schools not originally enrolled in the study were invited from local networks and randomized. In total 14 schools from all five main regions of Denmark were recruited for the study. From these schools all students in 6^th^ and 7^th^ grade classes (n = 869) were invited to participate in LCoMotion by a letter describing the study, the measurements, the randomization procedures and the consent form. All students, parents and teachers were then invited to a meeting at the school, where the scientific background and a full description of the study was given. Eighty-seven percent of the parents gave consent for their child to participate in the study (n = 757). The study was approved by the ethics committee of the region of Southern Denmark (S-20130104) and registered at clinicaltrials.gov (NCT02012881) (10/10/2013).

**Figure 1 Fig1:**
[figure not shown]
**Flowchart of schools in LCoMotion.**

### Intervention components

The intervention "package" in LCoMotion consisted of three main components:*Active Learning*. Participating classes’ primary teachers, and other interested teachers received supplementary training in delivering activities involving PA during academic subjects. The supplementary training consisted of a 3 hours course on one day. Focus was on practical tools to incorporate PA in the different subjects. All teachers were expected to register these activities using an "activity watch" hanging in each class room. The primary teacher of each class reported the total number of minutes used on "active learning", as well as the number of times that the teacher initiated PA in academic subjects, to the research team every week by text messages (see Outcome measures).*Physically active recesses.* Teachers and a selected group of students received supplementary training on how to conduct moderate to vigorous physical activities in recess with their students or peers. This course was partly with teachers and students together and partly with the two groups separated. The course was delivered on one day on each school and lasted 4 hours. Furthermore, all intervention schools received a bag with equipment for these activities, e.g. different types of balls, Frisbees, pins etc.*PA home work.* Students received a booklet with different activities lasting about 10 minutes each. They had to select one activity each day and register how many days they carried out an activity. Each month the teachers collected these booklets and distributed new ones with other activities. In the end of the intervention, there was a competition between classes of having most activities done.

Furthermore, during the third month of the intervention, all intervention classes received materials regarding a cycling commuting competition in the form of posters in the classrooms and information via the school’s intranet. All intervention classes competed for the highest frequency of cycle commuting during two weeks. Results were registered by the short message service (SMS) tracking system (see below).

All participating schools (principals and involved teachers) made an oral agreement with the research staff about endeavor to ensure that all participating student had 60 minutes of PA on all school days during the intervention. No guidelines on how to distribute the 60 minutes of daily PA were given. The practical implementation was therefore completely decided and administrated by the teachers and schools. This is also the case in the new Danish school reform, which intends to implement 45 minutes of PA every day in the school setting to all students [19].

### Data collection procedures and staff training

Prior to both baseline and follow-up testing all research personnel was trained by members of the research team on the assessment of mathematics skills, cognitive function, cardiovascular fitness, anthropometrics and self-assessment of pubertal status. Pilot tests of the flanker task and the mathematics test were conducted (see Outcome measures).

Data collections were performed at the participating schools in a gym and in the classrooms, except for the flanker task, which was performed in smaller rooms with a maximum of four students present at the same time.

### Outcome measures

#### Primary outcome

##### Cognitive function

Cognitive function was evaluated using a computer-based modified Eriksen flanker task [26]. An arrow pointing to the right “>” will require a right-handed response and an arrow pointing to the left “<” will require a left-handed response. These two response-eliciting stimuli are flanked by an array of other arrows that are congruent (>>>> > or < <<<<), or incongruent (>><>> or <<><<) to the centrally placed target stimulus. The incongruent condition is found to cause a delay in response time as well as a decrease in accuracy relative to the congruent condition, mainly because it requires greater amounts of inhibitory control to overwrite the stimuli induced by the distracting flankers. The congruent and incongruent conditions were randomly introduced. Participants completed one practice block of 20 trials to train the participants in what was expected, and to identify any problems they had in understanding and performing the test. If this test was not satisfactory, another practice block was completed, and this was repeated until the tester was certain whether the participant had understood the task correctly. Subsequently two blocks consisting of 75 trials each were presented for 120 milliseconds (msec) followed by a response window of 1350 msec. A random inter-stimulus interval of 1250 – 1550 msec separated each trial and a break of 30 seconds separated each block of trials. The entire test could be completed within 8 minutes. Students were instructed to respond as quickly and as accurately as possibly. The outcomes for the test were reaction time (RT) to the stimulus of the arrow on screen (msec) and accuracy (percentage of possible trials where the correct response was selected). Calculation of interference scores (incongruent – congruent) for both RT and accuracy will allow for interpretation of the flanker effect as the difference in speed and accuracy of information processing during the congruent and the incongruent trials [27]. Performance on the flanker task is unknown in a general population of adolescents in the midst of puberty. The progression through puberty could be of importance (though a similar progression in the control group and the intervention group would be expected) to both outcome measures (accuracy and RT) [27]. A pilot study was therefore conducted prior to the baseline testing on the study age group, and the flanker task was accordingly adjusted, in order to elicit a response accuracy of around 70 – 80% in the incongruent trials.

### Secondary outcomes

#### Academic skills

Academic skills were assessed by a mathematics test consisting of 50 questions of varying difficulty matching the requirements of 6^th^ and 7^th^ grade curriculum, respectively. No aids were permitted in the mathematical skill testing. A modified version (only numbers were changed) was administered at follow-up measurements. Students were allowed 45 minutes to complete the tests. The math tests were scored by the research staff. A pilot study was conducted and the mathematics skill tests were validated against a standardized math-test often used in the Danish school system to asses mathematics skills at the individual level in different age-groups [28]. A correlation coefficient of 0.87 (p < 0.001) was found between the standardized and the applied test.

### Physical activity (PA) measurements

PA levels of participants were assessed by accelerometry before and during the intervention. GT3X and GT3X + devices (ActiGraph LLC, Pensacola, FL, USA) were distributed by research staff to students at schools with the instruction to wear the devices on the right hip every day during a seven day period. Devices were distributed on Mondays or Tuesdays during November/December 2013 (before intervention) and during March 2014 (third month of the intervention). Accelerometer type was randomly selected at the student level and assessment periods were balanced between control and intervention schools. Due to a shortage of devices one intervention school did not receive accelerometers, as this school entered the study just prior to baseline testing. Furthermore, accelerometers were only distributed in four of five, four of six and three of four classes at another three schools.

Outcomes for PA levels will be mean counts/min during all assessed minutes as well as time (minutes) spent in different intensity domains (sedentary, light, moderate, vigorous PA). These parameters can furthermore be investigated in segments of the day (school time, recess, and leisure-time) as class-specific time tables were collected at both assessment periods. These segments were all components in the LCoMotion intervention and it will thus be possible to investigate whether the intervention caused any changes in PA during the different segments of the day.

### Cardiorespiratory fitness

Aerobic fitness was measured with the Andersen intermittent running test [29]. Two parallel lines 20 m apart were made on the floor. Subjects ran from one line to the other. They had to touch the line on the floor with one hand, turn around and run back. Music signaled 15 seconds of running and 15 seconds of rest. Participants had to stop immediately at the signal. This procedure was followed for 10 minutes giving an overall running time of 5 minutes. Subjects were told to run as fast as they could in order to cover the longest possible distance. This distance in meters was the test result, which has been validated against direct measures of maximal VO_2_-uptake [29, 30]. The test has also been found to have a fairly high reliability [30].

### Anthropometric measures and puberty assessment

Body height was measured without shoes to the nearest 0.5 cm using Harpenden stadiometer (West Sussex, UK). Body mass was measured in light clothing to the nearest 0.1 kg using an electronic scale (Tanita BWB-800, Tokyo, Japan). Waist circumference was measured to the nearest 0.5 cm with an anthropometric tape, at the level of the umbilicus. Sexual maturation was assessed by self-report using a scale of pictures of pubic hair for both sexes and of breast and genital development for girls and boys, respectively, according to the development divisions presented by Tanner [31]. Furthermore, girls had to report if they had started having menstrual periods.

### Short message service (SMS)-tracking quantifying the intervention elements

Every second week for the entire intervention period information on compliance with the intervention elements was collected using SMS-tracking on mobile phones (Automatic text messaging). Students at intervention schools received a message every second Friday asking how many times the last week;they had participated in programmed recess activitiestheir teachers had initiated physical activities in the academic subjectsthey had conducted their PA homework.

Once a month both intervention and control students were asked about bicycling to and from school the past week.

Main class teachers in all intervention classes were sent two questions each week;how many minutes the class had been physically active (both as planned recess activities and in academic subjects) in the past week following the “activity watch”how many times they themselves had initiated physical activities in academic subjects

For all messages both for students and teachers, if they were not answered, a follow-up message was send after 24 hours and again after 72 hours. If the message was not answered after that, or answered in text or other invalid ways, students or teachers were contacted by the research team by phone to clarify facts.

### Questionnaires

Three different questionnaires were administered; one for participating students, one for the parents or guardians, and one for main class teachers in all participating classes. All questionnaires were paper based.

The questionnaire for students contained a total of 29 questions and was administered on the test day at the school or by the teachers one or two days after the test day. The questions covered activities in recess, self-assessed school performance, relations to classmates, teachers, friends and family, motivation for school, PA in leisure time, sedentary behavior, mode of transportation, sleeping habits, diet (short), smoking habits and alcohol consumption. These items were categorized into four domains (school time, intrinsic factors, leisure-time activities and dietary habits). The questionnaire for parents contained 29 questions on their child’s health including diagnosed syndromes or illnesses, specifically mental illnesses and need for special education. Questions on ethnicity, household income and education, and parental assessment of the child’s academic skills were also included in the questionnaire. The parent questionnaire was delivered to the students on the test day and brought home to the parents with a pre-paid return envelope. Only one parent or guardian for each student was requested to answer the questionnaire. After 3-4 weeks all parents were reminded to fill out and return the questionnaire by a message on the school’s intra-net. Those parents who had not returned the questionnaire after 6 weeks had a new questionnaire resent. The majority of questions in both students’ and parent’s questionnaires had previously been used in other (inter)national surveys about children and adolescents’ health and PA habits (e.g. [32–34]).

Questionnaire for main class teachers was delivered by the end of the intervention, but before the follow-up testing and contained questions regarding the amount of planned activities during recesses and the amount of physical activities during academic subjects. This was done in order to compare the quantity of these elements, as the SMS-tracking is only used for quantifying intervention elements in the intervention schools (except for bicycling which was assessed in both intervention and control schools).

#### Statistical considerations

Sample size calculation was done prior to recruitment of schools. Conventional two-sided levels of statistical power (0.8) and level of significance (0.05) were used. Calculation was done based on expected differences between intervention and control group in one of the primary outcomes; accuracy in the flanker task. An intervention with the duration of the LCoMotion intervention was hypothesized to result in an effect size of approximately three percent points (personal communication with [name] about effect size and standard deviations). To lower the assumed cluster effect schools were grouped based on their grade point average from the final examination 2011/2012. Assuming a cluster effect of 0.01 and an average number of students per school of 80, the calculations showed that a minimum of 11 schools (5 control and 6 intervention schools) were required, with a total number of 680 students. Analyses were performed with statistical software STATA version 13.

The effect of the intervention will be tested using multilevel mixed effects models adjusted for relevant possible confounding factors, e.g. sex, age, baseline value of the variable, family socioeconomic status etc. Because of the cluster structure of data, schools and classes will be included as random effects in the analyses.

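### The sample-size statement is internally inconsistent: 11 schools, 80 students per school and 680 students cannot all hold, and without an SD the 80% power cannot be checked

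*Protocol article*

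**What the plan says.** The calculation is in the protocol article under Statistical considerations, which says it was made before schools were recruited.

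- Error rates: "Conventional two-sided levels of statistical power (0.8) and level of significance (0.05) were used".
- Outcome: "one of the primary outcomes; accuracy in the flanker task".
- Difference to detect: "an effect size of approximately three percent points".
- Standard deviation: no value is printed. The text cites only a personal communication "about effect size and standard deviations".
- Clustering: "Assuming a cluster effect of 0.01 and an average number of students per school of 80".
- Result: "the calculations showed that a minimum of 11 schools (5 control and 6 intervention schools) were required, with a total number of 680 students".

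The section states no allowance for non-consent, absence or dropout, and no rule that adds schools to the calculated number. The only participation figure elsewhere that bears on this is the observed consent, under Recruitment and randomization: "Eighty-seven percent of the parents gave consent for their child to participate in the study (n = 757".

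**The concern.** Cluster size, number of clusters and total are tied by multiplication: once two are fixed, so is the third. Here all three are printed together and the product misses the total by 200 students, which is too much for rounding.

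This affects more than presentation. The cluster size sets the design effect, and the design effect with the total and the SD sets the power. If the cluster size or the total is uncertain, so is the basis of the 80% claim. A reader would normally settle the matter by running the calculation and seeing which total comes out. Without the SD that is not possible. The Discussion places the study against a shortage of properly powered school trials, so the basis of its own power should be reproducible.

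**Working it through.** **Inputs.** All from Statistical considerations: two-sided alpha 0.05 (z = 1.960), power 0.80 (z = 0.842), difference 3 points, 80 students per school, 11 schools (5 control, 6 intervention), total 680. The cluster effect of 0.01 is read as the intraclass correlation (ICC); this is an assumption. The SD is not given.

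**Step 1: try to reproduce the stated total.**

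- 11 × 80 = 880 (400 control + 480 intervention), not 680. The gap is 200 students, and 200 / 680 = 29%.
- Keep 680 and 11 schools: 680 / 11 = 61.8 per school.
- Keep 680 and 80 per school: 680 / 80 = 8.5 schools, so 9, or 10 with equal arms.

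**Step 2: look for a step that would link the figures.**

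- Loss allowance: 680 analysable students out of 880 needs a loss of 1 − 680 / 880 = 22.7%. A 20% loss would give 680 / 0.8 = 850 students, or 10.6 schools, which rounds up to 11. Neither allowance is stated. The observed 13% non-consent would give 680 / 0.87 = 782 students, or 9.8 schools, which rounds up to 10.
- One extra school per arm: 8.5 + 2 = 10.5, which rounds up to 11. This rule is not stated either, and 11 schools of 80 would still hold 880 students.

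**Step 3: effect on the design effect.** Design effect = 1 + (m − 1) × ICC.

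- m = 80: 1 + 79 × 0.01 = 1.79.
- m = 61.8: 1 + 60.8 × 0.01 = 1.61.

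**Step 4: back-solve the SD that gives 80% power.** SD = 3 / [(1.960 + 0.842) × √(DE × (1/n1 + 1/n2))], with students split 5:6 between control and intervention.

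| Figures kept | n1, n2 | DE | √(DE × (1/n1 + 1/n2)) | Implied SD |
|---|---|---|---|---|
| 680 students, 80 per school | 309, 371 | 1.79 | 0.1030 | 10.4 |
| 680 students, 11 schools | 309, 371 | 1.61 | 0.0977 | 11.0 |
| 11 schools, 80 per school (880) | 400, 480 | 1.79 | 0.0906 | 11.8 |

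The first row applies the 6:5 split to what would be 8.5 schools. With equal arms of 340 it still gives 10.4.

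**Step 5: what each SD would mean for 11 schools** (normal approximation, 5 v 6 schools).

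- SD 10.4: schools of 80 give about 89% power; 680 students spread over 11 schools give about 84%.
- SD 11.8: schools of 80 give 80%; 680 students over 11 schools give about 74%.

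So the same sentence fits a design above its power target or one below it, depending on a number that is not printed.

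**The case against.** The strongest reply is that the mismatch does not show the requirement to be wrong. That stands. 680 / 1.79 = 380 students before clustering, or 190 per arm, which is a coherent standard calculation at an SD of about 10.4. Eleven schools of 80 would then exceed the target. An allowance for loss, or a rule adding schools, may have been applied and left out of a condensed article.

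It can also be said that the two minima printed were both exceeded: 14 schools took part, and 757 or 759 students had consent. That stands as well. The sentence is also retrospective, and neither the outcomes nor the analysis model depends on it.

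A reader might go further and infer three things that the document does not support:

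- *That 880 is the true requirement and 680 the error.* The figure 880 appears nowhere in the article, and without the SD neither total can be tested.
- *That the 757 or 759 students fall short of 880.* This takes 880 as the target and compares head counts while ignoring cluster size. With 759 students in 14 schools, m = 54.2 and the design effect is 1.53. The effective number is 759 / 1.53, about 495, against 880 / 1.79, about 492. At SD 11.8 and a 6:5 split, that gives about 80% power. The actual 234 v 525 split is less favourable, but that is a separate matter which the Discussion discloses.
- *That the trial is underpowered.* Any such figure depends on an SD obtained by first assuming that 880 is right.

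What the reply does not remove is the inconsistency. The three figures are printed together, and no stated step joins them. This is not detail left to a fuller document.

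**Conclusion.** The point holds as an internal inconsistency and a calculation that cannot be reproduced. At 80 per school, 11 schools hold 880 students, 200 more than the 680 stated. Keeping 680 means either 61.8 students per school or 8.5 schools. The design effect is 1.79 or 1.61, and the SD needed for 80% power ranges from 10.4 to 11.8, according to which figures are kept.

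It is not established which of the 11, the 80 or the 680 is at fault, whether a step went unreported, or whether true power lies above or below 80%. The SDs rest on reading the cluster effect as an ICC, on equal school sizes, and on a normal approximation that ignores the small number of schools. The mismatch in Step 1 needs none of these assumptions. The matter deserves correction because it underlies the power claim, but it does not threaten the conduct or analysis of the trial.

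**What to change.** Re-run the calculation from the original inputs and replace the sentence with one consistent set: SD of flanker accuracy, ICC, students per school, design effect, number of schools per arm, total students, and any allowance for non-consent, absence or dropout. State which figure is the requirement, and whether the total counts students invited, consenting or analysed. If schools were added as a margin, say so. Then give the power that follows from the corrected set.

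The cost is one corrected paragraph. The restated power may come out higher or lower than 80%. No change to enrolment, outcomes or analysis is needed.

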**Table 1 Tab1:** **Response rates (%) for all consenting participants**

Variables	Intervention schools	Control schools	All schools combined
	(n = 234)	(n = 525)	(n = 759)
Anthropometrics (height, weight, waist circumference)	89%	91%	91%
Pubertal status	89%	90%	89%
Cognitive test	93%	93%	93%
Mathematic test	94%	90%	92%
Fitness test	88%	81%	83%
Student questionnaire	95%	89%	91%
Parental questionnaire	89%	88%	88%
Accelerometer*	89 (73)%	84 (72)%	86 (72)%

*Not all students did accelerometer measurements for assessment of physical activity. In total accelerometers were distributed to 84% of all students (n = 193 and n = 445 in intervention and control schools, respectively). Participation rate is calculated from returned accelerometers with at least one valid day of measurements (≥10 hours) relative to total number of accelerometers distributed. Numbers in brackets show the percentages of all participants with consent.

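### The mixed-model test rests on 14 randomised schools and states no allowance for so few clusters; with large-sample inference its type I error would exceed 5%

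*Protocol article*

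**What the plan says.** Under Study design, the unit of allocation is the school: "The clusters consisted of participating schools". Under Recruitment and randomization, "In total 14 schools from all five main regions of Denmark were recruited for the study". Table 1 gives 234 consenting students in intervention schools and 525 in control schools, 759 in all.

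Under Statistical considerations, the analysis is fixed in these terms: "The effect of the intervention will be tested using multilevel mixed effects models", adjusted for covariates such as sex, age, baseline value and socioeconomic status, and "schools and classes will be included as random effects in the analyses". The level comes from the sample size paragraph: "Conventional two-sided levels of statistical power (0.8) and level of significance (0.05) were used". That paragraph assumes an ICC of 0.01 and arrives at a minimum of 11 schools. Stata 13 is named as the software.

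The article does not name the estimator (maximum likelihood or REML), the reference distribution (normal or t), a degrees-of-freedom method or a small-sample correction. It neither announces a normal-reference test nor rules a correction out.

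**The concern.** Modelling school and class as random effects is the right structure for this design. It does not by itself make the 5% level true. The treatment effect is a comparison between two groups of schools, so its precision depends on a between-school variance estimated from 14 units. Adding students or a class level gives no further information about variation between schools.

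Large-sample inference treats that variance as known. With 14 schools it is poorly known, and maximum likelihood also tends to underestimate it. The test then rejects too often and the intervals cover too little. A borderline result on flanker accuracy or reaction time could be declared positive when a correctly calibrated test would not support it. The same holds for mathematics, fitness and physical activity wherever schools truly differ.

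Two features of the trial add to this. Schools were grouped by examination grades before allocation, and adjusting for those groups would use up between-school degrees of freedom. Most large schools also fell in the control arm, so the arms differ markedly in size.

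**Working it through.** **The plan's own figure.** The only calculated figure is the sample size. The target difference is stated ("hypothesized to result in an effect size of approximately three percent points"), but the standard deviation is not. With 80 students per school and ICC 0.01 the design effect is 1 + 79 × 0.01 = 1.79, so 680 students correspond to 680 / 1.79 = 380 independent ones. Equal arms, 80% power and a 3-point difference then imply a standard deviation of about 10.4. The stated size can be neither confirmed nor refuted without that input, and nothing below depends on it.

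**Step 1: degrees of freedom.** 14 schools − 2 arm means = 12. For the planned minimum, 11 − 2 = 9.

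**Step 2: analytic size of a normal-reference test.** If the statistic follows a t distribution but is compared with 1.96:

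- 12 df: P(|t| > 1.96) = 7.4%, interval coverage 92.6%. Correct critical value 2.179; 2.179 / 1.960 = 1.11, so correct intervals are 11% wider.
- 9 df: P(|t| > 1.96) = 8.2%, coverage 91.8%. Correct critical value 2.262, ratio 1.15.

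Maximum likelihood is worse. In the simplest balanced case it divides the between-school sum of squares by 14 instead of 12, so the standard error shrinks by √(12/14) = 0.926. The effective cut-off is 1.96 × 0.926 = 1.815, and P(|t| > 1.815) on 12 df is 9.5%.

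**Step 3: simulation under the null.** Inputs from the article: 14 schools, 234 and 525 students by arm, ICC 0.01 as the planning value. Assumed: schools split 7/7 or 6/8 (intervention/control); school sizes spread evenly from 0.4 to 1.6 times the arm mean; a school random intercept only, without class level or covariates. There were 3,000 runs per setting, so the Monte Carlo standard error is about 0.4 to 0.6 points. Rejection rates at nominal 5%, as 7/7 split then 6/8 split:

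| ICC | ML, normal | REML, normal | REML, t(12) | School-mean t-test |
|---|---|---|---|---|
| 0 | 3.9%, 4.5% | 3.5%, 4.1% | 2.2%, 2.4% | 5.3%, 5.4% |
| 0.01 | 7.6%, 7.8% | 6.3%, 6.8% | 3.8%, 4.9% | 5.3%, 6.0% |
| 0.03 | 9.3%, 10.1% | 7.2%, 8.0% | 4.9%, 5.7% | 5.1%, 6.2% |
| 0.05 | 9.3%, 8.4% | 7.0%, 6.8% | 4.8%, 4.6% | 4.8%, 4.4% |
| 0.10 | 9.2%, 9.3% | 7.0%, 7.1% | 4.6%, 5.1% | 4.4%, 5.2% |

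**Step 4: with the planned class level.** A further simulation with a class random effect (1,000 runs per setting, school and class sizes assumed) gave 7.2-8.5% for ML with a normal reference, 5.7-7.0% for REML with a normal reference, and 3.6-5.7% for REML with t(12). The inflation is somewhat smaller but remains, and the t reference still removes it.

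**The case against.** The strongest reply is that the article is silent, and silence is not a plan. Estimator and degrees-of-freedom method are details that a condensed article commonly leaves to an analysis plan, and that plan is not at hand. REML with a t reference is itself a multilevel mixed-effects model and fits the quoted sentence. This stands, and it is why the point is conditional. A reader might infer from the missing correction, or from the named software, that a normal-reference test is planned. The article names no command or option, so the documents do not support that inference.

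It does not dispose of the point. The article goes beyond a general intention: it fixes the model class, both random-effect levels, the significance level and the number of clusters. For that combination the usual large-sample test does not hold its stated level, and a better method is available at little cost.

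Three other stronger readings also fail:

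- That p-values for every outcome will overstate the evidence. The inflation depends on estimator and ICC. Under REML at the planning ICC of 0.01 it is only 1 to 2 points, and near ICC 0 the normal-reference test is below 5%. The article gives no ICC for the secondary outcomes.
- That a school variance estimated as zero makes the model treat students as independent. Class is also a random effect, so within-class correlation is still modelled.
- That the school effect might be dropped from the model. The article already says that it will be included.

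**Conclusion.** The point holds in conditional form and is of moderate severity. With 14 randomised schools and no stated allowance for that number, large-sample inference from the planned model would have a true type I error of roughly 7-10% under maximum likelihood and 6-8% under REML for ICC 0.01 to 0.10, with 95% intervals about 10% too narrow (1.960 / 2.179 = 0.90). At ICC near zero there is no inflation.

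The result rests on assumed schools per arm, school sizes and class sizes, and on models without the planned covariates. The analytic figure of 7.4% on 12 df needs none of the size assumptions and points the same way. If an analysis plan already specifies a between-school reference distribution, the point is closed.

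**What to change.** State in the analysis section that the model is fitted by REML and that the intervention effect is referred to a t distribution with between-school degrees of freedom: about 12 for 14 schools, fewer if school-level strata are adjusted for. Kenward-Roger or Satterthwaite degrees of freedom serve the same purpose. If the software version does not offer any of these, make a school-level t-test on baseline-adjusted school means the confirmatory test; the unadjusted version held 4.4-6.2% across the settings in the table.

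The cost is a sentence or two of text and a few lines of code. Intervals become about 11% wider, with some loss of power, and the REML t(12) test is conservative (about 2%) if the ICC is near zero. The article says that data analysis was not yet complete, so the choice should be recorded before the outcome comparisons are seen, where that is still possible.
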